## Abstract

**Background:** Despite the rapid advance of neonatal care, bronchopulmonary dysplasia (BPD) remains a significant burden for the preterm population, and there is a lack of effective intervention. Stem cell depletion because of preterm birth is regarded as one of the underlying pathological mechanisms for the arrest of alveolar and vascular development. Preclinical and small-sample clinical studies have proven the efficacy and safety of stem cells in treating and preventing lung injury. However, there are currently no randomized clinical trials (RCTs) investigating the use of autologous cord blood mononuclear cells (ACBMNC) for the prevention of BPD in premature infants. The purpose of this study is to investigate the effects of infusion of ACBMNC for the prevention of BPD in preterm neonates <28 weeks.

**Methods:** In this prospective, randomized controlled double-blind multi-center clinical trial, 200 preterm neonates <28 weeks gestation will be randomly assigned to receive intravenous ACBMNC infusion (5 × 10^7^ cells/kg) or placebo (normal saline) within 24 h after birth in a 1:1 ratio using a central randomization system. The primary outcome will be survival without BPD at 36 weeks of postmenstrual age or at discharge, whichever comes first. The secondary outcomes will include the mortality rate, other common preterm complication rates, respiratory support duration, length, and cost of hospitalization, and long-term outcomes after a 2-year follow-up.

**Conclusion:** This will be the first randomized, controlled, blinded trial to evaluate the efficacy of ACBMNC infusion as a prevention therapy for BPD. The results of this trial will provide valuable clinical evidence for recommendations on the management of BPD in extremely preterm infants.

**Clinical Trial Registration:** ClinicalTrials.gov, NCT04440670, registered 06/18/2020, prospectively registered, https://clinicaltrials.gov/study/NCT04440670?term=NCT04440670&rank=1 (Additional File 2).

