#### Secondary Objectives

The secondary objectives of this trial are (1) to compare the infant mortality rate at 36 weeks of postmenstrual age; (2) to compare the rate of other common preterm complications included intraventricular hemorrhage (IVH), necrotizing enterocolitis (NEC), retinopathy of prematurity (ROP), respiratory distress syndrome (RDS), ventilation-associated pneumonia (VAP), hypoxic ischemic encephalopathy (HIE), late-onset sepsis (LOS), and anemia; (3) to compare the duration of mechanical ventilation and oxygen therapy in the two groups; (4) to determine re-intubation rate and time return to birth weight (BW); (5) to compare the duration of antibiotic usage; and (6) to determine the long-term outcomes after a 2-year follow up, including anthropometric characteristics, respiratory outcomes, and neurodevelopmental outcomes via standardized neurological examination.

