### Outcome Measures

*Primary outcome measure:*

- The frequency of BPD or death in at 36 weeks of postmenstrual age or discharge home whichever comes first.

*Secondary outcome measures:*

- Mortality rate- Incidence of BPD- Incidence of other preterm complications including IVH, PVL, NEC, ROP, RDS, VAP, LOS, and anemia [all clinical diagnoses will be defined according to a standard references (16)].- Duration of hospitalization.- Duration of mechanical ventilation and oxygen therapy- Frequency of re-intubation.- The time (days) return to BW.

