#### Follow Up

All the infants will be followed until the corrected age of 2 years old, the following parameters will be recorded.

- Anthropometric characteristics: weight, length, and head circumference.- Respiratory outcomes including the occurrence of wheezing, asthma, nocturnal cough, supplemental oxygen requirement, and rehospitalization because of pneumonia.- Degree of neurodevelopmental impairment via standardized neurological examination [using the revised Brunet-Lézine [RBL] global developmental quotient score (16)], and other major neurodevelopmental outcomes including cerebral palsy, seizures, auditory impairment, and visual impairment (Table 2).

**Table 2 T2:** Contents and points of data capture: Standard Protocol Items: Recommendations for Interventional Trials (SPIRIT) schedule of enrolment, interventions, and assessments.

**Visit**	**Screening**	**Intervention**	**Follow up**	
	**V1**	**V2**	**V3**	**V4**
Time point	born	Within 24 h after birth	36 weeks of postmenstrual age	Corrected age of 2 years old
Informed consent form	√			
Screening the subject	√			
Demographic information	√			
Inclusion/exclusion criteria	√			
Get random number	√			
Cord blood process		√		
Vital signs	√	√	√	
Chest radiographs		√		
Pulmonary surfactant replacement		√		
Mechanical ventilation	√	√		
Arterial blood oxygen saturation	√	√		
Laboratory tests	√	√	√	
Blood routine test	√	√		
Blood gas	√	√		
Safety outcomes		√	√	√
Record adverse events		√	√	√
Postnatal steroid use		√	√	√
Surgical closure of patent ductus arteriosus		√	√	
Blood products use		√	√	
Bronchopulmonary dysplasia			√	
Other preterm complications			√	
Duration of hospitalization			√	√
Anthropometric Characteristics			√	√
Respiratory Outcomes				√
Neurodevelopmental outcomes				√

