### Statistical Analysis

Statistical analyses between the two groups will be performed using an unpaired two-tailed Student's *t*-test or Chi-squared Test as appropriate. A logistic regression model will be used for the entire study population (i.e., without removing deaths) to adjust for the effect of treatment on primary outcome according to baseline characteristics and events known to affect the occurrence of BPD (i.e., gestational age, birth weight and other characters that are different in two groups after initial analysis), and to investigate the effect of treatment on the following outcomes: extubation rates, severe adverse events, and death before discharge. The Breslow-Day test and Corchran-Mental-Haenszel (CMH) test will be used to adjust the data derived from different participating centers. The results will be reported as odds ratio (OR) with 95% confidence intervals (CI). All statistical tests will be two-tailed and a *p* < 0.05 will be considered statistically significant. All statistical analysis will be performed using SPSS 21.0 (IBM).

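### One unadjusted two-sided p<0.05 rule covers the 15 listed secondary outcomes, and about 31 if every named item is tested; efficacy claims of significance should be confined to the primary test

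*Protocol article*

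**What the plan says.** The Statistical Analysis section of the protocol article fixes sidedness and threshold in one sentence that covers every test: "All statistical tests will be two-tailed and a" p-value below "0.05 will be considered statistically significant". The sentence is not limited to the primary outcome.

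Outcome Measures names one primary outcome, "The frequency of BPD or death in at 36 weeks of postmenstrual age or discharge home whichever comes first". Its secondary list opens with "Mortality rate- Incidence of BPD- Incidence of other preterm complications including IVH, PVL, NEC, ROP, RDS, VAP, LOS, and anemia" and continues with length of stay, ventilation and oxygen durations, re-intubation and time to regain birth weight.

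Other sections name more. Secondary Objectives aims "to compare the rate of other common preterm complications", with hypoxic ischemic encephalopathy among them, and adds duration of antibiotic use. The Abstract adds cost of hospitalization. Follow Up lists items to be recorded up to a corrected age of 2 years, for example "Respiratory outcomes including the occurrence of wheezing, asthma, nocturnal cough, supplemental oxygen requirement, and rehospitalization because of pneumonia". The Abstract and Secondary Objectives both class the long-term outcomes as secondary.

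The article does not rank the secondary outcomes, call them exploratory or make claims on them depend on the primary result.

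**The concern.** A threshold that labels any test result significant, applied to a long unranked list, gives chance many opportunities to produce a reportable effect. If the primary comparison were null, nothing in the stated rule would prevent a secondary result with p<0.05 from being presented as a statistically significant benefit. The Abstract says that "The results of this trial will provide valuable clinical evidence for recommendations on the management of BPD in extremely preterm infants", so such a claim could carry weight.

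The article's own history makes this more than theoretical. The Background section reports that the group's earlier comparison found no significant difference in BPD, but significant reductions in ventilation time (p = 0.028) and oxygen need (p = 0.047). The Sample Size section then describes the infusion as effective in shortening respiratory support, citing the group's own and others' work. The article does not say which outcome was primary in that earlier study or whether its p-values were adjusted. The reference numbers in the Sample Size section also do not include the one attached to those p-values, so the link is suggestive only. The durations of ventilation and oxygen therapy are secondary outcomes again here, under the same rule.

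**Working it through.** The article states no error rate for the secondary outcomes as a set, so there is no figure of its own to reproduce. The only stated input is the two-sided 0.05 level per test.

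**Step 1: count the outcomes.**

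- Outcome Measures: mortality and BPD (2) + eight complications (8) + hospital stay (1) + ventilation and oxygen durations (2) + re-intubation (1) + time to birth weight (1) = **15**.
- Follow Up: 3 anthropometric + 5 respiratory + 5 neurodevelopmental (the developmental quotient, cerebral palsy, seizures, hearing, vision) = 13. Running total 15 + 13 = **28**.
- Hypoxic ischemic encephalopathy and antibiotic duration (Secondary Objectives) and cost (Abstract): 28 + 3 = **31**.
- Statistical Analysis also names extubation rates, severe adverse events and death before discharge, which could raise the count to 34. They are not used below.

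**Step 2: independent tests, no effect on any outcome.** The chance of at least one p<0.05 is 1 − 0.95^m:

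- m = 15: 1 − 0.95^15 = 0.537
- m = 28: 1 − 0.95^28 = 0.762
- m = 31: 1 − 0.95^31 = 0.796

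The expected number of such results is 0.05 × m, that is 0.75, 1.40 and 1.55. This expectation does not depend on correlation.

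**Step 3: correlated tests.** These outcomes are surely correlated, but the article gives no correlations. I assumed normal test statistics with a common correlation ρ:

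P(at least one) = 1 − ∫ [Φ((1.96 − √ρ·c)/√(1−ρ)) − Φ((−1.96 − √ρ·c)/√(1−ρ))]^m φ(c) dc

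| Assumed ρ | 15 outcomes | 28 outcomes | 31 outcomes |
|---|---|---|---|
| 0 | 54% | 76% | 80% |
| 0.2 | 50% | 70% | 73% |
| 0.3 | 46% | 64% | 67% |
| 0.5 | 36% | 49% | 51% |
| 0.8 | 20% | 25% | 26% |

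**Step 4: beneficial direction only.** With 0.025 per test and independence:

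- m = 15: 1 − 0.975^15 = 0.316
- m = 31: 1 − 0.975^31 = 0.544

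At ρ = 0.5 these fall to about 18% and 26%.

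**The case against.** The strongest reply is that this is a condensed article whose analysis plan is not shown, and that ranking or labelling secondary outcomes is commonly left to that plan. The sentence in question can be read as a per-test convention, and the article does separate one primary outcome from those it calls secondary. Much of this stands: the missing hierarchy is not in itself a fault here. What remains is that the article states a rule of significance for all tests. An analysis plan that confined such claims to the primary outcome would have to depart from that sentence.

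A reader might infer more than the article supports:

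- **That a chance finding is likely.** For the 15 listed outcomes the figure exceeds one half only near independence. It is 36% at a correlation of 0.5, and close independence is implausible for outcomes such as mortality, hospital stay, ventilation and oxygen durations.
- **That 31 tests are planned.** Outcome Measures and Follow Up together give 28; the other three come from the Abstract and Secondary Objectives. The 13 two-year items are to be recorded, and no separate test of each is specified.
- **That the stated 5% is wrong.** It is a per-test level and correct as such. The article never offers it as an error rate for a family of tests.
- **That the primary result is compromised, or that the investigators plan to rescue a null primary with a secondary finding.** The secondary tests leave the primary test's level untouched, and the article announces no such plan.

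The figures also count chance harms as well as benefits, and chi-squared tests on rare events can run below their nominal level, so the real rates may be somewhat lower.

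**Conclusion.** The point holds as a modest one about interpreting secondary outcomes. The stated rule allows any secondary result with p<0.05 to be called statistically significant. With no effect on any outcome, the chance of at least one such result is about 20–54% over the 15 listed outcomes and 26–80% over 31. The second range applies only if every named item is tested. Both rest on an assumed common correlation between 0.8 and 0, on tests that hold their nominal level, and on counting each complication and duration singly. Even the lowest figure is well above what a reader would expect of a set of claims labelled at 5%. The primary inference, the design and the sample size are unaffected.

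**What to change.** In Statistical Analysis, limit the significance sentence to the primary outcome and add a statement on the rest, for example:

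*For efficacy, statistical significance (two-sided p<0.05) will be claimed only for the single primary comparison. Secondary and 2-year outcomes are supportive or exploratory. They will be reported as effect estimates with 95% confidence intervals that are not adjusted for multiplicity, and will not be used for efficacy claims. Safety outcomes, including death, late-onset sepsis, NEC and severe IVH, will be reported and reviewed for harm regardless of the primary result.*

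The last sentence matters because those four events appear under Safety Assessment as well as, in whole or in part, among the secondary outcomes, and the change must not mute a harm signal. A short fixed sequence tested after a significant primary result is a possible alternative but a debatable trade-off. It should use only outcomes already listed, and it must not gate the review of safety.

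The cost is wording only, in the protocol and any analysis plan, best settled before unblinding. No patients or data are added. The section already calls for odds ratios with 95% confidence intervals, so reporting changes little. The downside is that an isolated secondary p<0.05 can no longer be called a significant benefit.

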## Discussion

BPD is still a major complication of prematurity. Currently, therapy for BPD includes non-invasive ventilation strategies, inhaled nitric oxide, antioxidants, vitamin A, caffeine, and corticosteroids, however, these strategies are mainly palliative and do not address the underlying structural changes involved in BPD including the reduced numbers of alveoli, blood vessels, and prominent fibrosis of the lungs (24–29). Stem cells are showed to have beneficial effects on both treatment and prevention of BPD in several preclinical and clinical settings (16–19, 30–34). Cord blood MNCs are rich in stem cells. As a convenient and safe source of stem cells, it could provide regrowth to underdeveloped lung tissue of preterm infants by providing more stem/progenitor cells. In addition, its paracrine effects help to improve lung function, vascularization of the airways, and reduce fibrosis, and therefore have considerable potential for reducing lung injury in preterm infants (35–40). However, few studies have evaluated the effects of ACBMNC infusion for prevention of BPD in extremely preterm infants.

The outcome of our study would be a major step forward solving this problem. To our knowledge, this would be the first clinical trial to assess ACBMNC infusion soon after birth in extremely preterm neonates in terms of the rate of BPD and other prematurity-related complications. Considering the novelty of the therapy and the randomized double-blinded characters of this study, it may take longer time to complete this trial. These may be potential shortcomings of the study.

## Conclusion

In conclusion, this randomized, placebo controlled, double blinded study aims to investigate the effects of ACBMNC for preventing BPD in extremely preterm infants.

## Ethics Statement

The studies involving human participants were reviewed and approved by [Guangdong Women and Children Hospital Ethics committee]. The legal guardian of participants provided written informed consent to participate in this study.
